### Study Conditions

Participants will be randomly assigned to the intervention group or the attention control (Digify) group. Both groups will log into their assigned platform (CarePair or Digify) twice per week and read 1 article per log-in (12 articles total across the intervention) for the 6-week study period. Participants will access their respective platform via their personal smartphone device.

### Intervention Group

Participants assigned to the intervention group will have access to the CarePair app. Over the 6-week study period, they will be instructed to log in twice per week to read and engage with 1 article per log-in session (eg, by rating, commenting, saving, or taking notes). Participants will also be encouraged, but not required, to explore and engage with service referrals available through the platform. Backend data will be collected to measure app engagement, including participants’ number of log-ins, time spent engaging with materials, specific content accessed, and feature interactions.

The onboarding process will direct caregivers to create a profile for themselves and their care recipients, choose an avatar, and select service preferences (eg, modality, cost, distance based on zip code, and time of the day). Users will also be prompted to complete a 12-item assessment (administered at pre- and postintervention)—the content of which was informed by studies 1 and 2 described above—to measure the primary domains caregivers reported needing assistance with. Each item begins with the stem “In your role as a caregiver, how much support do you need with…” followed by items such as “Understanding your care recipient’s brain change?” and “Dealing with your own feelings and worries?” Response options range from 1 (no need) to 4 (high need).

Following the initial onboarding session, users will be provided with an in-app tutorial that introduces the platform’s primary features (see Figure 1 for screenshots of the CarePair app interface). The *Home* page provides a personalized feed of resources curated algorithmically based on the user’s reported needs and preferences. The *Services* tab includes a catalog of local and virtual services tailored to caregivers’ profile preferences and assessment responses gathered during onboarding. The *Library* tab allows participants to browse through the app’s vetted ADRD- and caregiving-related resources, thematically organized by domain and relevance. Both the *Services* and *Library* pages allow users to add filters by category (eg, social support, legal, education, and grief).

**Figure 1. F1:**
[figure not shown]
CarePair app interface.

Further, caregivers can interact with resources by commenting, rating, saving, sharing, or note-taking directly in the app. Comments and ratings are visible to other caregiver users. To protect confidentiality, users are instructed during onboarding to create pseudonymous usernames and avoid sharing personally identifiable information. Research staff review account registrations and may modify usernames if they contain personally identifiable information. User-generated content is routinely monitored by research staff. Comments will be removed if they include identifiable information, misinformation, promotional content, or potentially harmful or inappropriate language. These procedures are intended to reduce privacy risks and support a safe user environment. Finally, caregivers can edit their profiles and needs assessment responses, manage settings, review notes and saved resources, and access a directory of national ADRD-focused organizations in the *Account* tab.

All information related to services and resources will be maintained by the study team via a secure database repository. Within the app, caregivers may also flag content that is inaccurate, inaccessible, or outdated for review by the investigative team.

### Control Group

Participants in the attention control group will access a digital folder of articles via Digify, a secure document-sharing platform that allows for controlled access of materials and user-engagement tracking on metrics, including log-ins, articles read, and time spent viewing articles. This folder contains most articles available in CarePair, all focused on ADRD and caregiving topics (3 articles with video components were excluded as these formats are not supported by Digify), but they are not organized by relevance or tailored to caregivers’ needs. Control participants follow the same engagement schedule as participants in the intervention group (ie, 2 log-ins per week for 6 weeks; read 1 article per session). Control activities are designed to match the intervention condition in terms of time commitment and interface interaction, and to ensure consistent engagement across groups while allowing for the isolation of the impact of CarePair’s delivery and personalization features. During onboarding, participants are provided with a deidentified username and password to access the Digify platform, along with step-by-step instructions on the use of the platform.

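### The control arm does not isolate CarePair's delivery and personalization: the arms also differ in service referral and assigned task, so the between-arm contrast estimates the effect of the whole package

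*Protocol article*

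**What the plan says.** In the protocol article, the Control Group section makes two linked claims. The first is matching: "Control activities are designed to match the intervention condition in terms of time commitment and interface interaction". The second is the inference this is said to permit, "allowing for the isolation of the impact of CarePair’s delivery and personalization features". Retention and Adherence repeats the matching claim, in terms of how often participants interact and how engaged they are.

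The control arm is a Digify folder with most of the CarePair articles, but "they are not organized by relevance or tailored to caregivers’ needs". The task is "2 log-ins per week for 6 weeks; read 1 article per session". The folder is also slightly smaller: "3 articles with video components were excluded as these formats are not supported by Digify".

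The Intervention Group section describes more than a tailored version of that folder. Participants are to "read and engage with 1 article per log-in session (eg, by rating, commenting, saving, or taking notes"). A Services tab lists local and virtual services fitted to the user's profile and needs assessment, and "Participants will also be encouraged, but not required, to explore and engage with service referrals available through the platform". The text after Figure 1 adds that "Comments and ratings are visible to other caregiver users" and that the Account tab holds a directory of national dementia-focused organizations.

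Study Conditions sets the same minimum schedule for both arms.

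**The concern.** To isolate delivery and personalization, the arms would have to be alike in everything else. On the article's own description they are not. The largest departure is service referral. Referral is not a way of delivering articles. Aims and Objectives gives greater knowledge and use of formal services as what CarePair is for, and the Theoretical Framework treats formal services as a route to better coping and self-efficacy, which is one of the outcomes compared.

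At stake is attribution. The secondary objective compares the arms on stress, depressive symptoms, anxiety and self-efficacy, and the exploratory objective passes the effect sizes to a future trial. If a difference is read as the isolated effect of tailored delivery when it may come from referral or from the interactive task, the next trial could be built around the wrong component. The Limitations section does not warn the reader of this.

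**Working it through.** The article gives no figure on this point, so the check is a side-by-side reading of the arms followed by a count of what the design can identify.

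**Step 1: the arms compared**

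| Feature | CarePair | Control | Where |
|---|---|---|---|
| Log-ins and articles | 2 per week × 6 weeks × 1 article = 12 | 2 per week × 6 weeks × 1 article = 12 | Study Conditions; Control Group |
| Article ordering | Tailored to needs and preferences | Untailored | Intervention Group; Control Group |
| Platform | App | Digify folder | Study Conditions |
| Service catalogue and national directory | Yes; referrals encouraged, optional | None described | Intervention Group |
| Assigned task | Read and engage, with peer-visible comments and ratings available | Read | Intervention Group; Control Group |
| Video articles | Included | 3 left out | Control Group |

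The first row is matched. The second and third are the differences that the isolation sentence names. The last three are further differences. Peer comments and ratings are counted within the assigned task, because rating and commenting are the article's own examples of engaging.

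The 12-item needs assessment is not counted as a difference: neither Table 1 nor the Caregivers' Needs section restricts it to the intervention arm.

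**Step 2: what the contrast identifies**

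For any one outcome, suppose for simplicity that component effects add. Write *d* for platform delivery, *p* for personalization, *r* for referral and directory, *e* for the engagement task with its peer features, and *v* for the video articles. The between-arm difference is

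Δ = *d* + *p* + *r* + *e* + *v*.

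Two arms give one such equation per outcome, with five unknowns. The isolation sentence needs Δ = *d* + *p*, that is *r* + *e* + *v* = 0. Nothing in the article supports that restriction. If effects interact instead of adding, the components are still less separable.

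**Step 3: does a generous reading rescue the sentence?**

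Suppose delivery features is read broadly enough to take in saving, note-taking and commenting, so that *e* joins *d*. The requirement then becomes *r* + *v* = 0. The video term is probably small: 3 items from a library of unstated size. The referral term cannot be waved away in the same manner, because it is CarePair's declared purpose.

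**Step 4: the matching claim**

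Equal log-in and article counts support matching on frequency. They do not support matching on interface interaction, because one arm is told to engage with each article and the other is told to read it.

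**The case against.** The strongest reply is that the sentence speaks jointly of delivery and personalization features and never claims to isolate personalization alone. On that view the in-app functions are delivery, fitting services to assessed needs is itself personalization, and the sentence says little more than that both arms get much the same articles on the same schedule while CarePair's features differ. The objectives and the Statistical Analysis section also evaluate CarePair as a whole, and no planned analysis assigns an effect to a component.

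Much of this stands. The package comparison is already what the objectives describe, and misattribution in the results is a risk, not something the protocol plans. What does not stand is the absorption of referral. How services are matched may be personalization, but having a catalogue of services at all is content, and controls are not described as receiving it in any form, tailored or untailored.

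A reader might also infer that extra time on the app could explain a difference. The article gives no figure for time in either arm, referral use is optional and the activities are stated as designed to match, so that is conjecture.

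Nor is the lack of a planned comparison of usage by arm a defect. Both platforms record log-ins, content accessed and time, and an article may leave such a table to the statistical analysis plan.

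**Conclusion.** The isolation claim and the interface-interaction part of the matching claim are not supported by the article's own description of the arms. The between-arm contrast estimates the effect of the full CarePair package against an untailored article folder on the same log-in schedule. Two differences carry the conclusion: referral with the directory, and the engagement task with its peer-visible features. The 3 video articles add little.

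The reach is limited. The primary objective, feasibility and acceptability, is unaffected. The trial is expressly not powered for efficacy, so what changes is how the secondary contrast and its effect sizes may be described and carried forward.

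The conclusion rests on one inference: that controls have no referral catalogue, directory or peer features. The Control Group section describes only a document folder and names none of these, but it does not say outright that they are absent.

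A reader might go further and conclude that the comparator is invalid or the trial needs redesign. The documents do not support that: package against attention control is a sound comparison, and the fault lies in the property claimed for it.

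**What to change.** Keep the comparator and change the wording in three places.

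1. In Control Group, replace the isolation clause with a statement such as: *the comparison estimates the effect of the full CarePair package (tailoring, service referral and interactive features) versus an untailored article folder on the same log-in schedule, and does not separate these components.*
2. In Control Group and in Retention and Adherence, limit the matching claim to log-in and article frequency.
3. In Limitations, add that the between-arm difference is a package effect and that the effect sizes passed to the next trial should be read that way.

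The cost is a few sentences and a less favourable claim about mechanism. The 80 participants (40 per arm), the procedures and the analyses are unchanged. Analysis is planned for August 2026, so the interpretation can be settled before results are known.

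Optionally, report log-ins, articles opened and time on platform by arm from the logs already collected. This would show how well attention was matched in practice.

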### Recruitment

Sample recruitment will be facilitated by the project’s study site using a multipronged outreach strategy targeting ADRD caregivers in the following locations: New York City, Long Island, and Westchester County, New York; Seattle, Washington; and Los Angeles, California. Recruitment strategies will include: (1) posting study flyers in high-traffic areas in the abovementioned cities; (2) study announcements made through community organizations; (3) ResearchMatch, a NIH-funded online registry that connects research volunteers with institutional review board (IRB)–approved studies; (4) digital outreach, including social media advertisements on platforms (eg, Facebook and Instagram); and (5) outreach to organizations provided as resources within the CarePair app. Additionally, individuals who have participated in prior studies and have provided consent for recontact will be approached to gauge interest and eligibility. Snowball sampling through community networks, social media, and currently enrolled participants will also be encouraged. All interested individuals will be directed to complete the study’s screening survey to determine eligibility.

### Ethical Considerations

This study was approved by USC’s IRB on September 10, 2025 (protocol#: UP-25‐00690). The study IRB approval letter can be found in Multimedia Appendix 1. The trial is registered on ClinicalTrials.gov (NCT06418971). The trial registration record includes all items from the World Health Organization trial registration dataset (Multimedia Appendix 2), including the primary registry name, trial identifying number, key eligibility criteria, target sample size, primary outcomes, secondary outcomes, funding sources, and sponsor details.

In accordance with the International Council for Harmonisation–Good Clinical Practice E6(R3) guidelines and applicable local regulations, trained IRB-approved research assistants (RAs) will obtain electronic informed consent via REDCap’s e-Consent platform after confirming participant eligibility.

During the virtual consent meeting, RAs will review the study purpose, study procedures, and participant rights (eg, the right to withdraw at any time without penalty) to support participant comprehension, and will encourage questions at any time. They will also explain what participation entails, including time commitments, responsibilities, and potential risks. As consent is an ongoing process, participants will be promptly informed of any protocol changes that could affect their willingness to continue. After the consent meeting, participants will be emailed a copy of the informed consent form signed by both themselves and the consenting RA. See Multimedia Appendix 3 for the informed consent form.

All study personnel are trained in human participants’ protection, confidentiality, and recruitment procedures. Data collection, sharing, and storage will comply with HIPAA and IRB regulations. Each participant will be assigned a unique study identifier, and all data will be stored in a secure, password-protected REDCap database accessible only to IRB-authorized personnel. To maintain confidentiality, all datasets will remain deidentified throughout the study, including during analysis and dissemination.

Participants will receive US $25 for each completed survey and US $20 for an optional interview, for a maximum total of US $70. All payments will be sent as Amazon digital gift cards.

### Data Management

All study data will be stored on a secure, password-protected server with multifactor authentication, accessible only to IRB-authorized study personnel. Supported by the Southern California Clinical and Translational Science Institute (CTSI), REDCap [44,45] will be used for participant tracking, survey data collection, and consent procedures. As a secure, web-based data management platform, REDCap enables the development of customized data management and capture systems with online entry forms, reporting tools, automated export procedures for seamless data download to common statistical packages, and procedures for importing data from external sources. This database system is also utilized for the provision of data to the IRB, NIH, and US Food and Drug Administration and includes robust security features, including role-based access controls, Institutional Lightweight Directory Access Protocol and Shibboleth single sign-on (SSO) authentication, and a complete audit trail of data entry and export activities. REDCap is hosted on CTSI-managed servers, which are backed up daily and support encrypted (SSL-based) connections. The platform is maintained nationally through a multi-institutional consortium led by the Vanderbilt University Clinical and Translational Science Award program.

### Randomization Process

After providing consent and completing the baseline survey, participants will be randomized to either the intervention or attention control group using REDCap’s randomization module. A stratified permuted block randomized design is utilized to enhance internal validity and minimize potential confounding variables. Randomization tables are generated by an RA, who is not involved in data collection or participant randomization, using a custom Python script.

To ensure demographic balance across study arms while accommodating the target sample size (n=80), randomization is stratified based on caregiver sex and race/ethnicity, resulting in 24 unique strata. Within each stratum, 25 permuted blocks of 4 are created, each containing 2 “intervention” and 2 “control” assignments, randomly shuffled using Python’s random shuffle() function to ensure unpredictability. The full table is compiled into a .csv file and uploaded to REDCap’s secure randomization module. Once uploaded, the allocation table is locked and inaccessible (ie, no longer visible or modifiable) to study staff. Participants will be randomized in real time via REDCap after stratification variables are entered (sex and race) to preserve allocation concealment and ensure balanced/methodologically sound group assignment. Once randomized, study staff are unable to change participants’ group assignments.

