**Methods:**

This pilot RCT will evaluate the feasibility, acceptability, and preliminary efficacy of CarePair. Eighty ADRD family caregivers will be enrolled and randomized in a 1:1 ratio to the intervention (n=40) or an attention control condition (n=40). Recruitment will be facilitated by the project study site located in an urban metropolitan area of the United States, targeting participants who report residing in and/or being in close proximity to any of the following locations: New York City, Long Island, and Westchester County, New York; Seattle, Washington; and Los Angeles, California. Primary feasibility outcomes include recruitment, retention, and completion rates; website usability; and intervention satisfaction. Exploratory analyses will assess preliminary efficacy on stress, depressive and anxiety symptoms, and self-efficacy.

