### Sample Size

This study proposes to enroll 80 ADRD family caregivers, randomized in equal numbers (n=40 per group) to either the intervention or attention control conditions. Consistent with stages 0-1B of the National Institutes of Health (NIH) stage model for behavioral intervention development [46], the primary goal of this pilot study is to establish the feasibility and acceptability of CarePair. Accordingly, the study is not powered to detect clinically meaningful differences in outcomes. A sample size of 40 participants per arm exceeds the upper limit recommended (n=35) for feasibility trials [43] and allows for adequate precision in estimating key feasibility parameters (recruitment, retention/attrition, and platform usability), which will inform prespecified progression (go/no-go) criteria for advancing to a full-scale RCT. This approach is consistent with methodological guidance for pilot and feasibility studies, which prioritizes the estimation of feasibility parameters over formal hypothesis testing or power-based sample size calculations [47-50]. Preliminary efficacy will be explored as a secondary aim to estimate effect sizes and associated CIs to guide the design of a subsequent, fully powered efficacy trial.

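### With 24 strata and blocks of 4 for 80 participants, the randomisation scheme cannot ensure a 40:40 split or balance in the rarer race/ethnicity strata

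*Protocol article*

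**What the plan says.** The Abstract (Methods) describes participants as "randomized in a 1:1 ratio to the intervention (n=40) or an attention control condition (n=40"), and the Sample Size section repeats "This study proposes to enroll 80 ADRD family caregivers, randomized in equal numbers (n=40 per group").

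The Randomization Process section gives the purpose of stratifying: "To ensure demographic balance across study arms while accommodating the target sample size (n=80"). It then states that "randomization is stratified based on caregiver sex and race/ethnicity, resulting in 24 unique strata" and that "Within each stratum, 25 permuted blocks of 4 are created", each holding two places per arm. It closes by saying that real-time allocation will "ensure balanced/methodologically sound group assignment". The levels of the two factors are not listed. The second factor is called race/ethnicity when the strata are defined, but race when the data entry step is described: "Participants will be randomized in real time via REDCap after stratification variables are entered (sex and race"). No minimisation, pooling of small strata or constraint on overall arm sizes is described.

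The Statistical Analysis section compares change between groups. It chooses covariates by examining how candidates such as age, education and kinship relate to the outcomes. It does not name the stratification factors as covariates.

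**The concern.** A permuted block guarantees balance only once it is full. With fewer people per stratum than places in a block, many strata finish part-way through one. Each leftover contributes a random difference between arms, and these differences add up over strata. The 25 blocks prepared per stratum prevent a stratum from running out of places but do nothing about unfinished blocks.

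What is at stake is accuracy of description more than the result. The protocol claims a property that the scheme lacks, so an ordinary outcome such as 43:37 would look like a departure from protocol. The scheme is also presented as suited to n=80, and a pilot meant to inform a larger multisite trial could pass it on. Finally, residual imbalance in sex or race/ethnicity is not dealt with by rule in the analysis as written.

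**Working it through.** **Inputs from the protocol.** N = 80, 1:1 allocation, 24 strata, block size 4, 25 blocks per stratum.

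**The plan's own figure.** 80 × 1/2 = 40 per arm. By symmetry this is also the expected arm size under the scheme, so the figure is right as an expectation.

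**Occupancy.** 80/24 = 3.33 people per stratum; 3.33/4 = 0.83 of a block. One full block in every stratum would need 24 × 4 = 96 people, more than 80. The table holds 24 × 25 × 4 = 2,400 places.

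**Imbalance from one unfinished block.** Let r be the number of people in the last block of a stratum. For r = 1 or 3 the arm difference is ±1 (variance 1). For r = 2 it is 0 with probability 2/3 and ±2 with probability 1/3 (variance 4/3). For r = 0 it is zero. If K is the mean number of strata that end on an unfinished block, the SD of the overall arm difference lies between √K and √(4K/3).

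**Simulation.** The spread of participants over strata is an assumption, since the protocol gives none. There were 20,000 runs per stratified scenario.

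| Assumed distribution | Unfinished strata (K) | Empty strata | Exactly 40:40 | SD of arm difference | Mean absolute difference | 43:37 or worse |
|---|---|---|---|---|---|---|
| Uniform over 24 | 18.4 | 0.8 | 17% | 4.5 | 3.6 | 27% |
| Skewed 2×12 (sex 75/25, largest race group 40%) | 13.5 | 8.3 | 20% | 3.9 | 3.0 | 19% |
| Very skewed 2×12 (80/20, largest 60%) | 11.4 | 11.0 | 23% | 3.5 | 2.7 | 15% |
| Skewed 3×8 (74/25/1, largest 45%) | 10.9 | 11.1 | 23% | 3.5 | 2.7 | 14% |
| Simple randomisation | n/a | n/a | 9% | 8.9 | 7.1 | 58% |

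The bounds agree: K = 18.4 gives an SD between 4.3 and 5.0, and K = 10.9 gives one between 3.3 and 3.8. Separate runs, including a 4×6 layout, widen the ranges to about 16-24% for exactly 40:40 and 12-27% for 43:37 or worse.

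**Demographic margins, skewed 2×12.** The SD of the arm difference within the two sexes is 3.0 and 2.5, against 7.7 and 4.5 under simple randomisation. In the largest race group it is 1.3 against 5.7. In the rarest groups it is 0.8 against 0.9, so almost nothing is gained there.

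**Coarser schemes, if used from the first participant.** Unstratified blocks of 4 always give 40:40 (80/4 = 20 full blocks). Stratifying by sex alone gives it in 63% of runs (SD 1.3). Four strata give it in 43% (SD 1.8).

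**Switching tables now.** The Results section reports 44 enrolled as of February 2026, leaving 80 − 44 = 36. Keeping those 44 allocations and moving the rest to sex only, or to sex by three race/ethnicity groups, changes the SD from 4.6 to 4.7-5.1 under uniform strata and from 3.9 to 3.8-4.2 under skewed strata. The old unfinished blocks stay and new ones are added.

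**The case against.** The strongest reply is that the harm is small, and most of it stands. Each arm is within 2 of 40 in 73-86% of runs, and no stratum can differ by more than 2. Sex and the larger race/ethnicity groups are clearly better balanced than without stratification. Three stronger readings should therefore be set aside.

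- **That balance is not delivered.** A reader might infer this from the average of 0.83 of a block. It is only an average: with realistic skew the common strata fill several blocks, and the gain disappears only in sparse strata.
- **That precision suffers.** A 45:35 split multiplies the standard error of a mean difference by √(1/45 + 1/35)/√(2/40) = 1.008. For one-arm usability or acceptability estimates, 36 instead of 40 people widens the interval by a factor of √(40/36) = 1.05, and a larger arm is equally likely. Thirty-six still exceeds the guideline of 35 cited in Sample Size.
- **That fixed blocks of 4 in an unblinded trial make allocation unduly predictable.** Sparse strata seldom reach the last places of a block. With full knowledge of past assignments, about 20-25% could be deduced under 24 strata, against 32% with sex-only blocks of 4. Allocation follows consent and the baseline survey, and the table is hidden from staff.

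It is also fair to say that covariate adjustment may be set out in an analysis plan that is not shown. The Statistical Analysis section does state its own selection rule, however, and that rule rests on observed associations.

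**Conclusion.** The point holds in a limited form. The scheme promotes balance but cannot ensure equal arms, or balance in the rarer race/ethnicity strata. An exact 40:40 split is expected in about 16-24% of trials and 43:37 or worse in about 12-27%, with 40 per arm still the expected size. The ranges rest on assumed stratum distributions, because the 24 strata cannot be rebuilt: 2×12, 3×8 and 4×6 all fit. That exact balance is not guaranteed follows from the block arithmetic and does not depend on those assumptions. The use of both race/ethnicity and race for one factor is a separate, plain inconsistency in the same section.

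**What to change.** Leave the running allocation table alone.

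- **Abstract and Sample Size:** state about 40 per arm, as a target.
- **Randomization Process:** say that stratification promotes balance and does not guarantee it in sparse strata. Use one definition of the race/ethnicity factor throughout.
- **Statistical Analysis:** adjust the between-group efficacy estimates for sex and collapsed race/ethnicity as prespecified main effects, whatever their observed association with outcome. If an analysis plan already does this, align the text with it.
- **Future trial:** use a coarser stratification (sex, or sex by at most three race/ethnicity groups) or minimisation.

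The cost is wording plus a few degrees of freedom: with two sex levels and three race/ethnicity groups, 1 + 2 = 3. Both factors are already collected at screening.
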